## Abstract

Cancer is a life-threatening illness affecting all dimensions of a person’s health. Cancer survivors must build resilience to face this adversity and continue their life projects. The present study explores the enablers, barriers, and strategies to build resilience among cancer survivors. This qualitative, descriptive exploratory study will use purposive sampling to recruit cancer survivors and healthcare professionals from two hospital centers in Lisbon and Tagus Valley. Interviews will be conducted until data saturation occurs. Data analysis will be performed using an inductive content analysis process with the help of the QDA Miner Lite database. The findings from this study will generate knowledge that may help stakeholders to identify effective strategies to build resilience among cancer survivors. By implementing strategies to foster resilience, healthcare professionals can potentially promote positive adaptations to cancer by strengthening resilience enablers and reducing the impact of barriers.

## Introduction

1.

Cancer is the second leading cause of death worldwide, responsible for more than 9.6 million deaths in 2018 (WHO, 2022). In 2020, there were 19.3 million newly diagnosed cancer cases worldwide (Sung et al., 2021). According to the data from the Global Cancer Observatory, Portugal recorded 60,467 new cancer cases and 30,168 deaths in 2020, with a 5-year prevalence rate of 1662.8 per 100,000 population (Global Cancer Observatory, 2021).

Cancer is a devastating disease that significantly impacts a person’s physical, emotional, and social well-being. The journey of cancer survivors is often filled with challenges such as physical side effects of treatment, emotional distress, financial burdens, and disruptions in daily life and relationships. However, many cancer survivors exhibit remarkable resilience and maintain a positive outlook despite this adversity. Building resilience is crucial for cancer survivors to continue pursuing their life goals and aspirations. Resilience is a concept that has gained increasing attention in the healthcare field. It refers to the ability to withstand adversity and bounce back from demanding and stressful life experiences (Wiig et al., 2020). Resilience involves upholding a stable path of healthy functioning over time, along with the ability to generate positive emotions and experiences despite challenging life events (WHO, 2017). Authors argue that resilience is not a specific characteristic but rather a multidimensional concept that implies experiencing a substantial threat or severe adversity and the ability to adapt effectively. Resilience allows the person to enhance their internal and external resources (Molina et al., 2014; Deshields et al., 2016) through a process that leads to developing a psychic construction suitable for social insertion despite the potential aggression (Luthar et al., 2000; Rutten et al., 2013).

There are numerous definitions of resilience (WHO, 2017). Despite their differences, the countless definitions indicate that resilience is linked to processes and skills that lead to positive individual and community health outcomes, notwithstanding serious threats and hazards (Bartley, 2006; WHO, 2017).

Several scales have been developed for measuring resilience. However, theoretic resilience frameworks are not related to attempts to measure resilience due to the inherit challenge of measuring the person’s adaptive capacity (Sturgess, 2016). Several authors argue that the different scales only measure characteristics of resilience and that it is possible to score well in some areas while scoring poorly in others (Connor and Davidson, 2003; Bonanno et al., 2011). When measuring resilience, individuals answer inquiries regarding their own experiences and perceptions. This assessment requires an awareness action (Sisto et al., 2019) where they need to identify their resources. Furthermore, other studies have associated resilience with personal characteristics such as self-efficacy, self-esteem, and optimism (Edward et al., 2019; Gao et al., 2019; Lee et al., 2019). There is also evidence that resilience is a process; therefore, a person can mobilize inner resources to achieve positive outcomes (Sisto et al., 2019; Stainton et al., 2019). There is also some consensus that resilience might be an intermediate rather than an outcome, demanding the mobilization of one’s inner resources to achieve positive well-being outcomes (Sturgess, 2016; Sisto et al., 2019; Stainton et al., 2019).

Researchers should consider resilience as a set of psychological phenomena that must be explored. These phenomena can be triggered and fade over the course of an individual’s life, manifesting in certain areas while being absent in others (Rutten et al., 2013).

Evidence supports the notion that resilience is not solely a fixed trait but rather a dynamic process that can be cultivated and developed through various interventions. This notion applies to individuals facing challenging circumstances, including cancer (Ludolph et al., 2019; Seiler and Jenewein, 2019; Üzar-Özçetin and Hiçdurmaz, 2019; Kim et al., 2021; Saleem et al., 2021; Laker et al., 2022; Sihvola et al., 2022; Vargas-Román et al., 2022). Moreover, cultivating resilience can enhance an individual’s ability to overcome future adversities (Ludolph et al., 2019; Seiler and Jenewein, 2019; Üzar-Özçetin and Hiçdurmaz, 2019). Several events directly linked to cancer can considerably disturb urvivors’ health and quality of life. Factors such as the type and stage of cancer, time of diagnosis, and prognosis of the disease can significantly disrupt their well-being (Sun et al., 2019; Festerling et al., 2022). Studies also show that the side effects of treatment changes in body image, social stigma, and the fear of recurrence also can disturb cancer survivors’ health and quality of life (Willems et al., 2016; Karimi et al., 2017; Hall et al., 2018; Melissant et al., 2019). There is also evidence that cancer survivors experience a high level of stress, anxiety, depression, and fear (Amigo Vázquez et al., 2011; Seib et al., 2018), which ultimately can lead them to a distressing experience that threatens their physical, mental, and emotional well-being (Silva et al., 2012). Furthermore, cancer patients may resort to negative coping strategies when confronted with emotionally challenging situations (Baghjari et al., 2017). Therefore it is vital to highlight that coping strategies can be taught through interventions (Lee et al., 2006). In this context, health professionals can play a crucial role by helping cancer survivors to build resilience. However, cancer survivors do not always receive the support they need (Perl et al., 2016). Interventions that foster resilience among cancer survivors have demonstrated positive outcomes in improving psychological well-being, enhancing coping mechanisms, and promoting adaptive responses to stress. A review of randomized controlled trials aiming to identify effective resilience-promoting interventions in cancer survivors has recognized the beneficial effects achieved by interventions based on positive psychology, supportive-expressive group therapy, behavioral therapy, or mindfulness, with considerable variation in individual effect sizes (Ludolph et al., 2019).

Psychosocial interventions, such as psychoeducation, counseling, and supportive care programs, are a valuable source of information, emotional support, and practical tools to navigate the challenges they encounter during their cancer journey. These interventions focus on enhancing patients’ knowledge about their illnesses, fostering effective coping skills, and promoting adaptive strategies for managing emotional distress (Ludolph et al., 2019; Seiler and Jenewein, 2019; Üzar-Özçetin and Hiçdurmaz, 2019; Kim et al., 2021; Saleem et al., 2021; Laker et al., 2022; Sihvola et al., 2022; Vargas-Román et al., 2022).

Evidence shows several factors that can act as enablers or barriers to resilience (Melillo and Ojeda, 2005; Fernandes et al., 2021a). A previous study among nursing personnel revealed that higher levels of concern about stigma were associated with lower levels of resilience (Hernandez et al., 2016). A prior study on caregivers of people with schizophrenia identified various barriers to family resilience, including lack of knowledge about the disease, social stigma, expressed emotion, involvement in the relationship, and blame (Melillo and Ojeda, 2005; Fernandes et al., 2021a). Furthermore, these factors might differ in various contexts, as the manifestation of these factors for one health domain does not influence others (Davydov et al., 2010).

There is a lack of studies exploring and understanding the enablers, barriers, and strategies involved in building resilience among cancer survivors. By gaining an understanding of these aspects, healthcare professionals can direct their efforts towards identifying solutions to address these factors and remove or reduce their impact. Hence, this study aims to explore the enablers, barriers, and strategies to resilience among cancer survivors using a qualitative design to gather further information about resilience to help healthcare professionals support this group of patients more effectively.

## Materials and methods

2.

### Study design

2.1.

Descriptive exploratory designs help summarize and understand an area of interest that has not been studied in depth in a specific context (Hunter et al., 2019; Doyle et al., 2020). The phenomena under study are the enablers, barriers, and strategies to resilience among cancer survivors. Considering the paucity of knowledge regarding this phenomenon, we will conduct a qualitative descriptive exploratory study.

We followed the consolidated criteria for reporting qualitative research (COREQ) checklist (Tong et al., 2007) to guarantee the quality of this study protocol.

### Time period

2.2.

September–October 2023–August 2024 (Gantt Chart Figure 1).

**Figure 1 fig1:**
[figure not shown]
Project schedule.

### Population and recruitment

2.3.

We will use purposive sampling to recruit participants from two hospital centers in Lisbon and Tagus Valley. This sampling method is widely used in qualitative research to identify and explore data related to the object of interest. It allows the researcher to collect data from the best-fit participants and consequently safeguard that the findings are pertinent to the research background (Palinkas et al., 2015).

We will select cancer survivors and healthcare professionals as participants to operationalize this research. By including cancer survivors as participants, we aim to capture their firsthand experiences and perceptions regarding resilience. These individuals have gone through the challenges of a cancer diagnosis, treatment, and the subsequent journey of survivorship. Their insights into the factors that have enabled their resilience, the barriers they have faced, and the strategies they have employed are invaluable for building knowledge regarding the phenomenon under study. Including healthcare professionals as participants is crucial as they play a significant role in supporting and caring for cancer survivors. Their expertise and experiences working with cancer survivors can shed light on the challenges patients face and the strategies they employ to foster resilience.

#### Phase 1

2.3.1.

The study population consists of cancer survivors.

For this investigation, we consider a cancer survivor as a person from the time of diagnosis until the end of life (National Cancer Institute, 2022).

#### Phase 2

2.3.2.

The study population comprises healthcare professionals (i.e., nurses, doctors, psychologists, and physiotherapists).

Researchers will purposefully select participants considering the cancer type, stage, and time of diagnosis (phase 1) and with different professions and ranges of time spent caregiving (phase 2) to include participants that will provide different lived experiences.

### Inclusion criteria

2.4.

#### Phase 1

2.4.1.

Be a cancer survivor;People aged 18 years and above;Willingness to participate in the study;Ability to understand, provide informed consent and comply with all the proceedings.

#### Phase 2

2.4.2.

Be a healthcare professional (i.e., nurses, doctors, psychologists, and physiotherapists);Previous experience in caring for cancer survivors;Pre-existing psychopathological disorder;Willingness to participate in the study.

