### Exclusion criteria

2.5.

Target population under 18, and an unwillingness/inability to understand, provide informed consent or comply with all the proceedings.

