### Data collection procedures

2.6.

We will contact eligible participants via telephone through the leading researcher who will present the research project, its aims, the concepts under study, and the importance of the participant’s collaboration. This will be followed by an email where we provide written information regarding the research project to allow participants to reflect on and analyze the concepts before deciding on participating in the study.

We will do the interviews individually and face-to-face in a private room at the hospital centers. Researchers will ensure the chosen location is noise-free in an environment that provides the participants privacy and comfort. No one else besides the interviewer and participants will be present during the interviews.

A nursing lecturer will conduct the interviews with a Ph.D. in Nursing Sciences, an experienced researcher and a skilled interviewer (Fernandes et al., 2021b, 2022a,c). The interviewer has no prior relationship with the participants.

Before the interview, the interviewer will remind the concepts under study and remind participants about the research aims and the importance of the participant’s collaboration, guaranteeing that all participants will sign the written informed consent. To capture the interview data accurately, each session will be digitally audio-recorded.

We will develop an interview guide to ensure discussion remains relevant to the study’s aims. The focus will consist of a set of open-ended questions to collect participants’ characteristics and perceptions, covering the following:

Phase 1 - the participants’ characteristics (sex, age, marital status, time of diagnosis, type, and stage of cancer) and their perceptions regarding enablers, barriers, and strategies to build resilience;Phase 2 - the participants’ characteristics (sex, age, professional experience, time of expertise in caring for cancer survivors) and their perceptions regarding enablers, barriers, and strategies to build resilience.

We will use open-ended questions with prompts. For example, “What is your understanding of strategies you can use to build resilience among cancer survivors? Can you tell me more about that?”

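### A pre-existing psychopathological disorder is listed as an inclusion criterion for healthcare professionals, so Phase 2 as written can enrol only staff who have one

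*Protocol article*

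**What the plan says.** Section 2.4.2 (Inclusion criteria, Phase 2) of the protocol article has four items. The first is "Be a healthcare professional (i.e., nurses, doctors, psychologists, and physiotherapists"). The other three follow in one run: "Previous experience in caring for cancer survivors;Pre-existing psychopathological disorder;Willingness to participate in the study".

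The Phase 1 list in 2.4.1 has no item on mental health: "Be a cancer survivor;People aged 18 years and above;Willingness to participate in the study;Ability to understand, provide informed consent and comply with all the proceedings".

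Section 2.5 gives one set of exclusion criteria, not divided by phase, and it does not mention psychopathology either: "Target population under 18, and an unwillingness/inability to understand, provide informed consent or comply with all the proceedings".

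Section 2.3.2 describes the Phase 2 population by occupation alone: "The study population comprises healthcare professionals (i.e., nurses, doctors, psychologists, and physiotherapists").

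**The concern.** Read as it stands, the list makes a mental disorder in the professional a condition of entry. The aims give no reason for that. The study asks about enablers, barriers and strategies for resilience in cancer survivors, and professionals are included as informed observers of survivors, not as people with illness of their own.

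Three things are at stake.

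- **Who is heard.** The study is purposive and has no fixed sample size, so eligibility and selection are its main control over whose views it reports. The literal rule would remove most of the intended informants and select the rest on a trait that may well colour how they see resilience.
- **Traceability.** Section 2.9 commits the researchers to a logical, documented decision process. If recruiters ignore or reinterpret the item, recruitment departs from the written criteria.
- **Disclosure.** Enforcing the rule would require staff to reveal a mental-health diagnosis to a researcher. The article states no purpose for that information and does not list it among the data collected.

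**Working it through.** The article gives no figure on this point, so there is none to reproduce. The check is a comparison of passages.

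**Step 1: is the item really an inclusion item?** It stands under the Inclusion criteria heading and the Phase 2 subheading. Experience with survivors comes before it and willingness to take part comes after it, and both are plainly requirements. Its position in one continuous list makes a text-extraction fault an unlikely explanation. No wording negates or qualifies it.

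**Step 2: does the rest of the article support it?**

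| Place | What it fixes for Phase 2 | Mental-health restriction? |
|---|---|---|
| 2.3, rationale | "Their expertise and experiences working with cancer survivors can shed light on the challenges patients face and the strategies they employ to foster resilience" | None |
| 2.3.2, population | Four professions | None |
| 2.3.2, selection | "with different professions and ranges of time spent caregiving (phase 2) to include participants that will provide different lived experiences" | None |
| 2.5, exclusions | Under 18; unwilling or unable to understand, consent or comply | None |
| 2.6, data collected | "Phase 2 - the participants’ characteristics (sex, age, professional experience, time of expertise in caring for cancer survivors") | None |

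No other section uses the item, gives a reason for it or records whether it was met.

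**Step 3: what sample does each possible meaning give?**

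| Reading | Eligible professionals | Effect on Phase 1 |
|---|---|---|
| Literal inclusion | Only those with a disorder | None |
| Exclusion placed in the wrong list | Only those without a disorder | None, unless it also applies there |
| Item meant for Phase 1 | No mental-health restriction | Survivors restricted |
| Stray line | No mental-health restriction | None |

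The first two readings have no one in common: every professional admitted under one is refused under the other. The article does not say which reading is meant.

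**Step 4: rough size, for illustration.** Let *p* be the share of otherwise eligible staff with such a disorder. The article gives no *p*, so 0.10 to 0.30 is assumed.

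- Share shut out by the literal rule = 1 − *p*: 1 − 0.10 = 0.90, and 1 − 0.30 = 0.70.
- Share shut out if an exclusion was meant = *p*: 0.10 to 0.30.

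The defect does not depend on these values. For any *p* below 1, the literal rule refuses professionals whom section 2.3.2 describes as the study population.

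**The case against.** The strongest reply is that this is an evident drafting slip that nobody would apply. No screening step, sampling dimension or collected characteristic refers to the item, which points to a slip and not a working rule. That is probably right about origin. It does not settle what was intended, and Step 3 shows that the candidate corrections lead to different samples.

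A second reply is that inclusion criteria routinely narrow a population description. Section 2.3.1 gives no age limit, yet 2.4.1 adds one, so the silence of 2.3.2 on mental health is not a contradiction in itself. This is fair as far as it goes. The inconsistency rests on the whole picture: no rationale, no selection dimension, no data item, and an opposite-seeming item absent from 2.5. The age limit, by contrast, is mirrored in 2.5.

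Third, a qualitative study does not seek statistical representativeness, and a percentage of a recruitment pool is not a study quantity. This stands. The harm is better described as an unexplained narrowing of perspectives, and the percentages only indicate scale. That a professional's own disorder would shape their view of resilience is likewise an inference, not something the article documents.

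Finally, the disclosure concern is conditional, because no procedure shown asks staff for a diagnosis. That also stands, and the burden arises only if the criterion is enforced.

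**Conclusion.** The concern holds. Section 2.4.2 makes a psychopathological disorder a requirement for Phase 2 entry. This conflicts with the rationale, population and selection text in 2.3, has no counterpart in 2.5, and could not be verified from the characteristics listed in 2.6. Every professional without such a disorder is ineligible as written. This is a positive statement in an operative eligibility list, not a detail left to a fuller document, and it should be corrected before recruitment.

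The conclusion rests on one ordinary assumption: that the items in an inclusion list are all required. The 70% to 90% range rests on an assumed prevalence and carries no weight in the conclusion.

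**What to change.** 1. Delete the psychopathological-disorder item from 2.4.2. Phase 2 eligibility is then profession, experience of caring for cancer survivors and willingness to take part. Informed consent is already required through 2.5, 2.6 and 2.10, but could be listed in 2.4.2 for parity with Phase 1.
2. If an exclusion was meant, state it in 2.5, say which phase it applies to, and give the reason and how it would be established.
3. If the restriction to affected staff was deliberate, justify it and change 2.3 and 2.6 to match.
4. Align 2.3.2, 2.4 and 2.5, and submit the corrected list to the ethics committee before recruitment.

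For the deletion, the cost is a one-line correction and an ethics notification, with no extra participants or procedures.

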### Exclusion criteria

2.5.

Target population under 18, and an unwillingness/inability to understand, provide informed consent or comply with all the proceedings.

### Data collection procedures

2.6.

We will contact eligible participants via telephone through the leading researcher who will present the research project, its aims, the concepts under study, and the importance of the participant’s collaboration. This will be followed by an email where we provide written information regarding the research project to allow participants to reflect on and analyze the concepts before deciding on participating in the study.

We will do the interviews individually and face-to-face in a private room at the hospital centers. Researchers will ensure the chosen location is noise-free in an environment that provides the participants privacy and comfort. No one else besides the interviewer and participants will be present during the interviews.

A nursing lecturer will conduct the interviews with a Ph.D. in Nursing Sciences, an experienced researcher and a skilled interviewer (Fernandes et al., 2021b, 2022a,c). The interviewer has no prior relationship with the participants.

Before the interview, the interviewer will remind the concepts under study and remind participants about the research aims and the importance of the participant’s collaboration, guaranteeing that all participants will sign the written informed consent. To capture the interview data accurately, each session will be digitally audio-recorded.

We will develop an interview guide to ensure discussion remains relevant to the study’s aims. The focus will consist of a set of open-ended questions to collect participants’ characteristics and perceptions, covering the following:

Phase 1 - the participants’ characteristics (sex, age, marital status, time of diagnosis, type, and stage of cancer) and their perceptions regarding enablers, barriers, and strategies to build resilience;Phase 2 - the participants’ characteristics (sex, age, professional experience, time of expertise in caring for cancer survivors) and their perceptions regarding enablers, barriers, and strategies to build resilience.

We will use open-ended questions with prompts. For example, “What is your understanding of strategies you can use to build resilience among cancer survivors? Can you tell me more about that?”

We will pilot-test the interview guide among participants and experts in qualitative research to ensure it is understandable and helpful in retrieving the required information. In addition, we will collect data to determine that the guide is sufficiently explicit, objective, and comprehensive and does not present questions that could be ambiguous or equivocal.

We estimate that the interview will take approximately 40–50 min.

